#### Practical advice

The intervention focusses on raising self-efficacy for being able to avoid drinking in social situations, if desirable.^50^ The participant will be asked to select 3 among 12 provided drinking situations that they consider most tempting and rank them. The situations are adapted from the adolescent version of the Drinking Refusal Self-Efficacy Questionnaire (DRSEQ-RA).^96^ According to the selection, a number of strategies will be offered for each of the selected drinking situations to provide participants with a tool kit necessary for engaging in and maintaining their behavioural goal.

#### Health-related information connected to substance use

Finally, the intervention programme includes health-related information associated with substance use. The information is provided optionally throughout the programme behind ‘read more’ buttons and also at the end of the programme. The information contains statements regarding risks connected to substance use that the participant can reflect on, as well as optional links for more information. There are also two frequently asked question sections about alcohol and cannabis, respectively, as well as information about how different substances may affect the individual, both physically and mentally. Finally, the information also contains cases, were the participant can read about some typical young persons who have used substances, why they used and what negative effects they have noted and why they chose to stop using.

### The control condition

The control group will receive the same general health-related information as the intervention group, that is, the additional information which is connected to the intervention programme.

### Statistical analysis

Randomisation checks of baseline variables regarding alcohol and other substances use and psychological state will be conducted using multivariate analyses of variance. To test the effectiveness of the intervention, we will assess whether participants in the intervention group to a greater extent report decreased substance use, sexual risk behaviours, perceived peer-pressure and improved mental health after 3 and 6 months, respectively, compared with participants in the active control group. Data analyses will consist of comparing outcome measurements with regards to within-group and between-group differences according to the intention-to-treat (ITT) principle in the primary analysis, accounting for all included participants regardless of whether or not they completed follow-up assessments. We will also perform per protocol analyses. The reason for choosing ITT in the primary analysis is the ambition to maintain the power of the study and also to avoid biassed results due to selection of those completing all follow-ups, as they may have special characteristics not representative for the whole study group, which might influence study results. The main analysis of effectiveness will use mixed effects regression models, which can be applied to both continuous and categorical outcomes and also non-normally distributed outcomes. Also, mixed-effects regression models are robust to missing data in longitudinal studies.^97^ In the current study, we assume a quite large dropout rate, based on previous research. For example, a meta-analysis comprising 17 studies of unsupported (fully automated) interventions for depression showed 74% dropout rate at post-treatment.^98^ Moreover, we expect data missing at random, which can be handled using mixed effects regression models. Separate models will be run to test each outcome, that is, alcohol consumption, binge drinking, frequency of alcohol consumption, amount of alcohol consumed a typical day when alcohol is consumed, average daily drinks per typical week, other substance use, mental health, sexual risk behaviours and perceived peer pressure at 3-month and 6-month follow-ups. Effect size will be calculated for the primary outcome variable (AUDIT-C total score). Potential moderators, including perfectionism, openness to parents, help-seeking due to mental health problems and socio-demographic and personal characteristics, (ie, sex, age, residence, occupation, school performance (for students) and parents’ education) will serve as covariates in analyses of intervention effects. If moderator effects are found, we will carry out post hoc analyses stratified by the detected variable.

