### Measures

All assessments will occur online. The selection of measures and associated instruments is based on the aim of the study and the theoretical base concerning factors influencing substance use. Based on results from the previous European WISEteens study,^38^ showing significant effects on alcohol consumption but not on other substance use, the primary outcome is alcohol use, measured at 3-month and 6-month follow-ups. Secondary outcomes include binge drinking, frequency of alcohol consumption, amount of alcohol consumed a typical day when alcohol is consumed, average daily drinks per typical week, at 3-month and 6-month follow-ups, other substance use, mental health, sexual risk behaviours and perceived peer pressure at 3-month and 6-month follow-ups. The moderating variables include perfectionism, openness to parents, help-seeking due to mental health problems and socio-demographic and personal characteristics, (ie, sex, age, residence, occupation, school performance (for students) and parents’ education).

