
### Randomisation

The study is double-blind, thus neither the participant nor the researchers will know which participant is allocated to the intervention or to the active control condition. After baseline assessment, the participants will be automatically randomised to one of the two study groups by a computer programme using an unrestricted randomisation protocol. Participants will then be informed about the name of their programme and given access immediately.

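### Baseline balance is to be tested by MANOVA and within-group change sits in the primary analysis, while the named covariates omit baseline AUDIT-C

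*Protocol article*

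**What the plan says.** All of this is in the protocol article; no separate analysis plan is at hand.

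- **Balance check** (Statistical analysis): "Randomisation checks of baseline variables regarding alcohol and other substances use and psychological state will be conducted using multivariate analyses of variance". No test level, decision rule or consequence is attached.
- **Allocation** (Randomisation): participants are randomised by a computer programme "using an unrestricted randomisation protocol", so there is no stratification or blocking on baseline drinking.
- **Comparisons** (Statistical analysis): "Data analyses will consist of comparing outcome measurements with regards to within-group and between-group differences according to the intention-to-treat (ITT) principle in the primary analysis".
- **Test of effectiveness** (same section): "we will assess whether participants in the intervention group to a greater extent report decreased substance use", and the comparator is the active control group. The Rationale and hypothesis section frames the hypothesis in the same way.
- **Model** (same section): "The main analysis of effectiveness will use mixed effects regression models, which can be applied to both continuous and categorical outcomes". How the baseline score enters is not stated.
- **Covariates** (same section): perfectionism, openness to parents, help-seeking, sex, age, residence, occupation, school performance and parents' education "will serve as covariates in analyses of intervention effects". Baseline AUDIT-C is not on the list.
- **Entry** (Screening and informed consent): a CRAFFT score of at least 2.

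**The concern.** Three stated choices pull away from a clean analysis.

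First, after computer randomisation any baseline difference is due to chance. A MANOVA tests whether chance produced it, which is already known. It rejects at its nominal rate whatever happens, and an omnibus test can pass over a modest imbalance in baseline AUDIT-C, the variable most likely to predict the outcome. With no consequence attached, the result also leaves room for choosing covariates after seeing the data.

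Second, participants are selected for a raised score on a substance-use screen. Drinking scores in both arms may then fall without any intervention effect. A significant fall within the intervention arm is therefore not evidence of effectiveness, and significance in one arm but not the other is a poor substitute for comparing the arms.

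Third, the baseline score is collected and unrestricted allocation does not balance it, yet the explicit covariate list leaves it out. Depending on the model actually fitted, precision may be given away.

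**Working it through.** **Sample size as stated.** The Recruitment section gives d = 0.2 and 800 participants. Two-sided 5% and 80% power are assumed, since neither is stated, with 1:1 allocation. Then n per arm = 2(1.960 + 0.842)² / 0.2² = 393, or 786 in total, close to 800. With 400 per arm power is 0.807. The target therefore matches a comparison with no baseline adjustment and no allowance for dropout.

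**Within-arm tests when there is no effect.** Assume SD = 1, full follow-up with 400 per arm, correlation r = 0.6 between baseline and follow-up, and the same fall of 0.1 SD in both arms. Neither r nor the fall is in the document.

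- Standard error of the mean change in one arm: √(2(1 − r)/n) = √(0.8/400) = 0.0447.
- Chance that one arm's change is significant: Φ(0.1/0.0447 − 1.960) = Φ(0.276) = 0.61.
- Chance of significance in the intervention arm only: 0.61 × 0.39 = 0.24.
- A two-sided 5% between-arm test rejects in that direction with probability 0.025.

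The result depends on the assumed fall and on the number followed up:

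| Common fall (SD) | Intervention arm only, 400 per arm | Intervention arm only, 104 per arm |
|---|---|---|
| 0.05 | 0.16 | 0.08 |
| 0.10 | 0.24 | 0.16 |
| 0.15 | 0.08 | 0.24 |
| 0.20 | 0.01 | 0.23 |
| 0.30 | 0.00 | 0.07 |

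The 104 per arm is 26% of 400, following the 74% dropout that the article cites as an example. Where the one-arm figure is small at larger falls, it is because both arms are usually significant (0.994 each at 0.20 SD and 400 per arm). That is no more informative about the intervention.

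**Precision from using baseline.** Take three visits, equal correlation r between them, SD = 1, n = 400 randomised per arm and m per arm with follow-up (the rest baseline only). For the 6-month between-arm effect:

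- arm means constrained equal at baseline: variance = 2(1 − r²)/m;
- free baseline means (change contrast): variance = 2(1 − r²)/m + 2(1 − r)²/n.

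Example at r = 0.5 with full follow-up: 1.5/400 = 0.00375 (SE 0.0612), against 0.00375 + 0.5/400 = 0.00500 (SE 0.0707), a cut of 25%. At 74% dropout: 1.5/104 = 0.01442 (SE 0.1201), against 0.01442 + 0.00125 = 0.01567 (SE 0.1252), a cut of 8%.

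| r | Full follow-up: SE free, constrained | Variance cut | 74% dropout: SE free, constrained | Variance cut |
|---|---|---|---|---|
| 0.3 | 0.0837, 0.0675 | 35% | 0.1412, 0.1323 | 12% |
| 0.5 | 0.0707, 0.0612 | 25% | 0.1252, 0.1201 | 8% |
| 0.7 | 0.0548, 0.0505 | 15% | 0.1013, 0.0990 | 4% |

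Power for d = 0.2 at r = 0.5 goes from 0.81 to 0.90 with full follow-up, but only from about 0.36 to 0.38 at 74% dropout. If the intended model already conditions on baseline or constrains the baseline means, the gain is near zero.

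**The case against.** The best defence is that the article already has the right test. Effectiveness is defined against the active control group, the hypothesis is framed that way, and the main analysis is a mixed model. Three stronger readings are tempting, and the document supports none of them.

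- *Within-group change replaces the between-arm test.* It does not. It is listed in addition, and nothing says that effectiveness will be concluded from significance within an arm.
- *The MANOVA is the plan's remedy for imbalance, or decides whether to adjust.* No remedy, threshold or consequence is stated. Even the use of p-values is inferred from the choice of method.
- *The plan loses precision.* The article never specifies an arm-by-time model with free baseline means. How baseline is parameterised is a detail that an analysis plan commonly holds, so its absence from an article is no error. The loss is conditional on the model, and under the heavy dropout that the authors expect it is small.

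It is also fair to say that selection is on CRAFFT while the outcome is AUDIT-C, with no correlation given, so the size of any regression to the mean is unknown. The randomised control group protects the between-arm contrast from it. Keeping participants who have baseline data only is already an aim of the stated intention-to-treat analysis, so it is not a new benefit of the constrained model.

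What remains is what the text does state: an uninformative balance test, within-group comparison given primary status, and a covariate list without the baseline outcome.

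**Conclusion.** The point holds in this limited form. The MANOVA check answers no useful question, within-arm change should not carry weight in the primary analysis, and the named covariates omit baseline AUDIT-C although a between-arm test is stated. None of this biases the planned between-arm estimate. The risks are misinterpretation and, possibly, lost precision.

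On misinterpretation, the chance of an intervention-arm-only result with no effect is about 0.24 under an assumed fall of 0.1 SD, r = 0.6 and 400 per arm, and it varies widely with the size of the fall. On precision, the variance saving is 35%, 25% and 15% with full follow-up, and 12%, 8% and 4% at 74% dropout, for r = 0.3, 0.5 and 0.7. That saving applies only if a free-baseline change contrast is intended. All correlations are assumptions, and the calculation is for a continuous, normally distributed outcome.

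**What to change.** 1. Replace the MANOVA randomisation check with a descriptive baseline table by arm, without tests.
2. State that within-arm changes are descriptive and that conclusions on effectiveness rest only on the between-arm contrast.
3. State that baseline AUDIT-C enters the primary mixed model, either as a response with arm means constrained equal at baseline, or as a covariate. With the covariate form, say how participants with baseline data only are handled, given the commitment to account for everyone included.
4. For the other outcomes, adjust for each outcome's own baseline in a form suited to its type. The Gaussian constrained model does not carry over unchanged to categorical or strongly skewed outcomes.

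The cost is wording in the analysis plan, plus some specification work for the non-normal outcomes. It uses the baseline assessment already planned and needs no further participants.

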### Rationale and hypothesis

The current study will add to existing evidence regarding the effectiveness of digital interventions aimed at reducing alcohol and other substance use among young people. We hypothesise that participants in the intervention group will report a significant reduction in substance use (primarily alcohol use), compared with an active control group receiving health information about various substances. A number of potential moderators will be assessed to confirm or contradict previous research on factors influencing the development of substance use patterns over time, and effects of prevention interventions in different target groups.

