## Methods and analysis

In order to evaluate the effectiveness of the digital screening and brief motivational intervention, a double-blind, two-arm, RCT study design is planned with baseline assessment at study entry and follow-up assessment at 3 and 6 months across a number of outcome variables. Figure 1 displays the trial design. We will also explore and test for moderator effects. To outline and report the current study we used Standard Protocol Items: Recommendations for Interventional Trials reporting guidelines.^69^

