Alcohol use, including the primary outcome, will be measured using two instruments. One of them is the short version of the Alcohol Use Disorders Identification Test (AUDIT-C),^76^ measuring frequency and amount of consumed alcohol and frequency of binge drinking, providing a widely used and valid index sum score for problematic alcohol use among adolescents.^75 77^ The other is the Daily Drinking Questionnaire (DDQ),^78^ measuring a variety of parameters of alcohol use in a typical week. Previous research has demonstrated that the DDQ is highly correlated with other measures of self-reported alcohol consumption.^79^ The primary outcome will be measured by AUDIT-C total score. The two measures of alcohol use complement one another in that the AUDIT-C primarily offers an indication of hazardous or harmful use,^80^ whereas the DDQ quantity measure (average daily drinks per typical week) will indicate the level of alcohol consumption in grams per week. Other substance use will be measured by a short version of the Drug Use Disorder Identification Test (DUDIT),^81^ including the first four items (DUDIT-C) which assess frequency of consumption of drugs other than alcohol, frequency of different types of drugs other than alcohol used at the same occasion (1 = never to 5 = *four or more times a week*) and number of occasions when drugs other than alcohol are consumed on a typical day of drug use (1 = zero to 5 = *seven or more)*. The DUDIT has been found to be effective in screening for drug-related problems in clinically selected groups,^82^ and both the DUDIT and the DUDIT-C have proven useful in the context of public health surveys in Sweden.^81 83^ Mental health will be measured by The WHO-5 Well-Being Index, which has demonstrated validity both as a screening tool for depression and as an outcome measure in clinical trials.^84^ This scale has been successfully applied across a wide range of study fields, translated into more than 30 languages, including Swedish,^85^ and found psychometrically sound. Changes in sexual risk behaviours will be measured by multiple choice questions on sexual behaviour under the influence of alcohol and/or other substances and unprotected sex, previously used in a survey among Swedish visitors at youth health clinics in Stockholm County.^86^ Changes in perceived peer pressure will be measured by two items retrieved and adapted from the peer pressure inventory.^87^ Perfectionism will be measured by two subscales of the Frost Multidimensional Perfectionism Scale.^88 89^ Openness to parents will be measured among participants who are up to 20 years old with questions about disclosure from Stattin and Kerr,^90–92^ slightly modified into statements to be compatible with the digital online format. Help-seeking due to mental health problems will be measured by dichotomous questions regarding if, and to what healthcare provider, the participant has turned for help. Additionally, background data will be asked for using multiple choice questions: sex (man, women, other), age (15, 16…25), residence (name of municipality), occupation (secondary school, upper secondary school, university, not student, working, practicing, unemployed, other), school performance (merit value for students) and parents’ education (secondary school, upper secondary school, university, don’t know).

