## Discussion of strengths and limitations

The current study has a number of strengths. The protocol describes a two-arm, double-blind, RCT, considered to be the most robust experimental design, controlling for selection bias and participant allocation bias and with the possibility to make causal inferences. Moreover, an active control condition, blinded to the study condition, controls for expectation, detection and performance bias. The collection and analysis of information on potential moderators, allowing for control of these factors, facilitates the understanding of the possible effects. Thus, the present study will contribute to the literature on digital substance use prevention interventions among adolescents and young adults in several ways. The choice to study a digital intervention can from a public health perspective be regarded as positive. Digital brief interventions have several advantages over face-to-face approaches, for example, the reduction of stigma around help-seeking for substance use and easy dissemination to large groups of people, which makes them cost-effective. Moreover, digital interventions have previously proven effective in addressing alcohol and other substance use in the general population and some studies have shown promising results also among adolescents and young adults.^99 100^ The current intervention is well grounded in theory and incorporates elements of MI and social influence theory that has been shown to be effective in reducing problematic substance use in prior research.^57^ Importantly, there are also some limitations to the current study. One limitation concerns selection bias and thereby external validity, as recruitment requires either that individuals click on our advertisements at social media to be considered for inclusion, or that they attend upper secondary schools or have been in contact with existing clinics, aware of the opportunity to participate in the study. Thus, our participants may have certain personality traits, or are especially prone to help-seeking compared with a broader audience. The exclusion of people not understanding Swedish is also a limitation with regard to generalisability.

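### Moderators are to be entered as covariates, which does not test moderation; two of them are not defined for every participant

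*Protocol article*

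**What the plan says.** The opening of Methods and analysis states the intention: "We will also explore and test for moderator effects". The Statistical analysis section gives the method. It lists "Potential moderators, including perfectionism, openness to parents, help-seeking due to mental health problems" and then "sex, age, residence, occupation, school performance (for students) and parents’ education", nine variables in all, and says that they "will serve as covariates in analyses of intervention effects". The next sentence reads: "If moderator effects are found, we will carry out post hoc analyses stratified by the detected variable". The article does not mention an interaction with treatment anywhere.

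The discussion of strengths presents the moderator work as an asset: "The collection and analysis of information on potential moderators, allowing for control of these factors". That describes adjustment.

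Two further statements matter. Under Measures, openness to parents is asked only of participants aged 20 or younger, although the trial enrols from 15 to 25, and school performance is a merit value for students. Under Statistical analysis, the primary analysis is by intention to treat and is to cover everyone enrolled, including those who miss follow-up.

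**The concern.** The stated method does not answer the stated question. A variable is a moderator if the difference between arms changes with its level. Entered as a covariate, it contributes a coefficient for its own association with the outcome, and the model still assumes one treatment effect for all. Someone following the text literally could mistake a strong predictor of drinking for a moderator and overlook a variable that does change the effect.

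The stratified step builds on this. Treatment tests run separately within strata tend to give a significant result in one and not in another by chance or through unequal stratum size. Without a test of the difference, this can be reported as an intervention that works in one group only.

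There is also a practical cost. A participant aged 21 to 25 has no openness score, and a non-student has no merit value. If both variables enter the effectiveness models, default handling drops those people. Mixed models cope with missing outcomes, not with covariates that do not exist for part of the sample.

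**Working it through.** **Inputs from the article.** Target sample 800; target effect d = 0.2 (Recruitment). Nine candidate moderators (Statistical analysis), or ten if perfectionism counts twice: "Perfectionism will be measured by two subscales". Dropout is described as quite large; 74% is cited as an example from automated depression interventions.

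**Assumptions, not stated in the article.** 1:1 allocation, two-sided 5%, 80% power, SD = 1, one follow-up without baseline adjustment, binary moderator.

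**The plan's own figure.** n per arm = 2 × (1.960 + 0.842)² / 0.2² = 392.4, so 393 per arm and 786 in total. This is within 3% of 800. With 400 per arm, SE = √(2/400) = 0.0707, z = 0.2/0.0707 = 2.83 and power is 81%. The 800 is thus matched by the overall effect, with no allowance for dropout.

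**What the two coefficients estimate.** Write the outcome as a + b·T + c·M + d·T·M, with T the arm and M a binary variable. With even allocation, a model that omits T·M estimates c + d/2 for M. The moderation parameter is d.

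- Prognostic only (c = 0.5, d = 0): the covariate coefficient is 0.5 with SE 2/√800 = 0.0707, so z = 7.07. Nothing is moderated, yet the term is almost certain to be significant.
- Moderation only (effect 0 in one half, 0.4 in the other; d = 0.4, c = −0.2): the covariate coefficient is −0.2 + 0.4/2 = 0. A real moderator is invisible.

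**Simulation of these two cases** (N = 800, 2,000 runs, share significant at 5%):

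| Case | Covariate term | Interaction term |
|---|---|---|
| Prognostic only | 100% | 6.5% |
| Moderation only | 4.5% | 79% |

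The 6.5% should be 5% by construction. A repeat with 20,000 runs gave 4.9% there and 81% in the lower right cell, so the excess is simulation noise.

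**Participants without a value.** The age distribution is not given. If those aged 21 to 25 make up 20%, 40% or 60% of the 800, then 160, 320 or 480 people have no openness score. With equal numbers at each of the eleven ages, it is 800 × 5/11 = 364.

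**Context: power once an interaction is tested.** For an even split, SE = √((2/n per arm) × (1/0.5 + 1/0.5)), twice the main-effect SE.

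| Followed up | SE | Power, 0.2 SD interaction | Power, 0.4 SD interaction |
|---|---|---|---|
| 800 (no dropout) | 0.141 | 29% | 81% |
| 560 (30%) | 0.169 | 22% | 66% |
| 400 (50%) | 0.200 | 17% | 52% |
| 208 (74%) | 0.277 | 11% | 30% |

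If nine independent interaction tests were each made at 5%, the chance of at least one false positive would be 1 − 0.95⁹ = 37% per outcome.

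**The case against.** The strongest reply is that the authors plainly mean to test moderation. They say so in Methods and analysis, and the trigger for stratifying is a moderator effect, not a significant covariate. The method wording is loose and does not rule out an interaction. Covariate entry also suits part of the stated purpose: the Rationale wants "to confirm or contradict previous research on factors influencing the development of substance use patterns over time", which is a question about predictors. Only the rest of that sentence concerns effects in different target groups. This stands in part. The text does not commit the trial to stratifying on every strong predictor, and a reader who infers that goes too far. But the one method stated remains the wrong one for the question, and an analysis plan that used interactions would depart from it.

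Three other inferences are tempting and are not supported:

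- **That the trial has almost no power for interactions.** Power is low for an interaction as large as the target effect. At 0.4 SD it is about 81% with complete data and an even split. The 74% dropout is a cited example, and the article claims no power for moderators.
- **That multiplicity is mishandled or the candidates are a fishing list.** All nine are named in advance, the stratified work is openly called post hoc, and a detection rule or multiplicity rule may sit in an analysis plan that is not shown. The 37% is therefore context and not a fault in the text.
- **That the primary result is compromised.** The AUDIT-C comparison does not depend on the moderator analysis. The one link is the possible loss of participants, and that arises only if the partly measured variables enter the effectiveness models.

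**Conclusion.** The point holds in a limited form. The covariate wording does not deliver the promised moderator test, and the stratified step rests on it. That a covariate term and an interaction answer different questions follows from the algebra and does not depend on the power assumptions. The simulated percentages belong to the two illustrative cases chosen.

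The risk of dropping participants is conditional. It needs openness or school performance to enter the effectiveness models with default handling of absent values, and its size depends on an age mix and student share that the article does not give.

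The power figures rest on the assumptions listed with them. Repeated measures or baseline adjustment would raise them somewhat. Uneven splits, many-category variables such as residence and occupation, and variables measured in a subset would lower them. With one fifth of participants in the smaller group and no dropout, they fall to about 21% for 0.2 SD and 62% for 0.4 SD.

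This should be corrected, but it is secondary: the primary inference stands without it.

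**What to change.** Replace the covariate wording with a statement that each potential moderator is examined in its own mixed model through a treatment-by-moderator (by time) interaction on AUDIT-C. Report each interaction as an estimate with a 95% confidence interval, and label the set exploratory. Show stratum-specific estimates only descriptively and beside the interaction, not as separate significance tests. Keep openness to parents and school performance out of the main effectiveness model. Analyse each as a moderator only in the participants for whom it is defined, and state that number.

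The cost is a few sentences, slightly more modelling and more cautious moderator claims. No change to data collection or sample size is needed.
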